## 9. Data management and biometrical evaluation

All clinical data will be recorded in specifically prepared forms to be incorporated later into an electronic database. In the database they will be combined with the results of the laboratory analyses.

For all quantitative parameters determined a test for normal distribution will be performed according to Kolmogorov-Smirnov. If normal distribution can be assumed, mean and standard deviation will be given for these parameters. For non normally distributed data median and interquartile range will be provided and data will be transformed appropriately prior to statistical analysis.

The repeated basal determination of blood markers of folate status is performed, as it is reasoned that both parameters undergo not only random variation, but there might be trends over time, after changes of dietary habits or physiological status. The effect of these trends should be attenuated by application of the average values of two measurements taken at different time points. This should become obvious from a better correlation of the averaged values compared to the individual values. A similar reasoning is behind the complete 24h urine collection, if there are short term variations in urinary concentration of total p-ABG or FIGLU extrapolation to total volume of excretion during 24 hours via urinary creatinine concentration is not adequate. If this is the case, there should be a closer relationship between the measured 24 h excretion of p-ABG and FIGLU with RBC folate than between the 24 h excretion estimated from the spot urine sample and RBC folate.

The major focus of statistical evaluation is a correlation and receiver operator characteristics (ROC) (Streiner et al, 2007) analysis between the determined circulating folate status markers and the urinary markers of folate status. Correlation analysis will be performed according to Pearson or Spearman. For ROC analysis classification into the lowest quartile as assessed with RBC folate will be set as "Gold Standard". Corresponding specificity, sensitivity, positive predictive value and negative predictive value will be determined for urinary total p-ABG and FIGLU excretion (measured and estimated 24 h excretion). Parameters will be compared in respect to the area under the ROC curve.

The obtained coefficients are the primary criterion for the applicability of the latter parameters as indicators of the subjects folate status. For a more detailed analysis of the data multiple regression analysis with RBC folate as the independent parameter and urinary excretion of total p-ABG or FIGLU as dependent variable including correction for other potentially confounding factors (e.g. vitamin B12, vitamin B6, age) will be performed. For these detailed analyses the support of an experienced biostatistician will be sought.

For evaluation of the time course of blood and urine markers of folate status repeated measures analysis of variance will be performed, with group allocation (high or low folate status according to RBC folate) as an independent factor. Furthermore, correlation analysis as described for the basal values will be performed, to investigate the suitability of urinary folate markers under conditions of a defined recent change of folate intake.

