#### **5. Participating subjects**

##### **5.1. Subject number**

The sample size estimation is based the correlation study. It is assumed that a correlation of at least 0.35 would be sufficient to use urinary total p-ABG or FIGLU as markers for

folate status. To detect such a correlation as statistically significant with a power 80% and  $\alpha$  of 0.05 samples from 49 subjects have to be analyzed (Uitenbroek, Daan G, Binomial. SISA. 1997. <http://www.quantitativeskills.com/sisa/distributions/binomial.htm>. (1 Jan. 2004). Thus, 50 subjects will be enrolled into the correlation study and from these participants for the intervention study will be selected.

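### A Kolmogorov-Smirnov test, applied marker by marker, sets the scale of the primary correlations; at n = 50 this can cost modest power and put compared coefficients on different scales

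*Protocol*

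**What the plan says.** Protocol section 9 (Data management and biometrical evaluation) says that for all quantitative parameters "a test for normal distribution will be performed according to Kolmogorov-Smirnov". Parameters taken as normal are summarised by mean and SD. The others get median and interquartile range, and their "data will be transformed appropriately prior to statistical analysis". On the correlation itself the section says: "Correlation analysis will be performed according to Pearson or Spearman". It gives no rule for choosing between the two. The variant of the normality test, its level and the transformation are not stated.

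The same section makes the resulting coefficients the primary criterion for whether the urinary markers are usable. It also draws conclusions by comparing coefficients: averaged against single blood values, and measured against spot-estimated 24 h excretion.

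Section 5.1 sets the size of the correlation part. It holds that "a correlation of at least 0.35 would be sufficient", with 80% power and α "of 0.05 samples from 49 subjects have to be analyzed"; hence "50 subjects will be enrolled into the correlation study".

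**The concern.** The rule makes the scale of the primary analysis depend on a pre-test, and the named test is a weak one. When mean and SD are estimated from the same 50 values and the usual critical value is kept, the test almost never rejects. A skewed marker can then be declared normal and stay untransformed.

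Skew is plausible here. The markers are positive concentrations and excretions, and section 5.2 admits supplement users in order to widen the folate range. If Pearson is then used on the raw scale, a few high values carry much of the coefficient, and power falls relative to the log scale.

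The gate also works on each parameter separately. Two versions of one marker that section 9 wants to compare can therefore fall on different sides of it, so that part of the difference between their coefficients comes from the scale.

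**Working it through.** **The plan's own figure.** Fisher z: n = ((z_α + z_power) / atanh(r))² + 3, with r = 0.35, atanh(0.35) = 0.3654 and z_power = 0.8416.
- One-sided α 0.05: ((1.6449 + 0.8416) / 0.3654)² + 3 = 49.3. This reproduces 49.
- Two-sided α 0.05: ((1.9600 + 0.8416) / 0.3654)² + 3 = 61.8, so 62.
- Power at n = 50: 81% one-sided, 71% two-sided.

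**Inputs to the check.** From the protocol: n = 50 and r = 0.35. Assumed, because the protocol gives no distribution: both markers log-normal with the same log-SD, correlation +0.35 on the log scale, normality tested at 0.05. An inverse correlation was not simulated.

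**Method.** 40,000 simulated samples per setting. A flagged variable is logged, an unflagged one is left raw, and Pearson's test follows. The critical value at n = 50 is 0.188 for the standard Kolmogorov-Smirnov (KS) test and 0.124 with the Lilliefors correction. Used with fitted mean and SD, the standard test has a true size of about 0.0001 instead of 0.05.

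Share of samples flagged as non-normal:

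| log-SD | skewness | standard KS | Lilliefors | Shapiro-Wilk |
|---|---|---|---|---|
| 0.2 | 0.61 | 0.3% | 17.5% | 32% |
| 0.3 | 0.95 | 1.3% | 34.0% | 58% |
| 0.5 | 1.75 | 11.1% | 70.9% | 93% |
| 0.6 | 2.26 | 23.0% | 84.4% | 98% |
| 0.75 | 3.26 | 45.9% | 95.0% | 100% |
| 1.0 | 6.18 | 80.2% | 99.5% | 100% |

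Two-sided power, %:

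| log-SD | raw Pearson | gated, standard KS | gated, Lilliefors | log Pearson | Spearman |
|---|---|---|---|---|---|
| 0.2 | 70.3 | 70.3 | 70.6 | 71.9 | 66.8 |
| 0.3 | 68.3 | 68.4 | 69.5 | 71.8 | 66.6 |
| 0.5 | 62.3 | 63.6 | 69.2 | 71.6 | 66.5 |
| 0.6 | 58.7 | 62.4 | 69.8 | 71.6 | 66.4 |
| 0.75 | 53.0 | 62.4 | 70.6 | 71.4 | 66.2 |
| 1.0 | 44.2 | 66.8 | 71.4 | 71.5 | 66.4 |

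At log-SD 0.7 the standard test flags 39% and the gated power is 63%.

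**Loss against logging in advance.** Standard KS: 71.8 − 68.4 = 3.4 points at log-SD 0.3, 71.6 − 63.6 = 8.0 at 0.5, 71.6 − 62.4 = 9.2 at 0.6, 71.5 − 66.8 = 4.7 at 1.0. Lilliefors: at most 2.7 points (at log-SD 0.4: 71.4 − 68.7). One-sided at log-SD 0.5 the standard gate loses 81.1 − 73.9 = 7.2 points.

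**Different scales.** The two variables in one correlation end on different scales with probability 2 × (share missed − share where both are missed). At log-SD 0.5 this is 2 × (0.889 − 0.790) = 20% with standard KS and 2 × (0.291 − 0.087) = 41% with Lilliefors. For two versions of one marker, assuming they correlate at 0.89 on the log scale, the gate splits them at log-SD 0.5 / 0.7 in 15% / 30% of samples with standard KS and in 28% / 11% with Lilliefors.

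Such a split moves the population coefficient. With log-SD s:
- both variables logged: 0.35;
- one raw: 0.35·s / √(exp(s²) − 1) = 0.328 at s = 0.5 and 0.308 at s = 0.7;
- both raw: (exp(0.35·s²) − 1) / (exp(s²) − 1) = 0.322 and 0.296.

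The compared coefficients share one variable. If that variable is logged, the split shifts the comparison by 0.35 − 0.328 = 0.02 or 0.35 − 0.308 = 0.04. If it is raw, the shift is about 0.01.

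**The case against.** A reader might infer that at n = 50 the rule misses most skewed distributions and sends them to raw Pearson. The protocol does not support that reading, for two reasons.
- Section 9 also permits Spearman, so nothing forces raw Pearson. If Spearman is used throughout, the gate has no effect on the coefficient.
- The text names Kolmogorov-Smirnov without a variant and does not exclude the Lilliefors correction. With that correction, at log-SD 0.5 and above, where raw Pearson loses 9 points or more, 71% or more of samples are flagged.

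Further objections stand in part. Assuming exact log-normality with r = 0.35 on the log scale favours the log analysis by construction, and some of the lost power is simply the smaller raw-scale correlation. Against Spearman in advance, the standard gate loses at most about 4 points (66.2 − 62.4 at log-SD 0.75). The area under the ROC curve does not change under a monotone transformation of the urinary marker, and the RBC folate quartile depends on ranks only, so that half of the main analysis is untouched.

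The test variant and the Pearson or Spearman choice may also be settled in an analysis plan that is not at hand, so their absence is not itself a fault. What remains is the rule the protocol does state: a marker-by-marker pre-test decides the scale of the primary coefficients.

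**Conclusion.** The point holds in a limited form. The stated rule hands the scale of the primary correlations to a weak, separately applied pre-test. If that test is the standard one with fitted mean and SD, and Pearson follows, the cost is about 3 to 9 points of two-sided power for log-SD 0.3 to 0.75. With Lilliefors it is under 3 points. The Lilliefors correction does not remove the risk of compared coefficients resting on different scales, although the expected shift is small (about 0.01 to 0.04 at log-SD 0.5 to 0.7). All these figures rest on the assumed log-normal shape.

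It would be wrong to read the distance from 80% to about 72% as an effect of the gate. That distance comes from testing two-sided at n = 50, whereas 49 subjects reproduces only one-sided. With logging in advance and a one-sided test, simulated power is about 81%. This is a modest improvement to the plan, and the planned analysis does not fail without it.

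**What to change.** In section 9, replace the test-driven choice with a scale named in advance: log-transform urinary total p-ABG and FIGLU excretion, serum folate and RBC folate, use Pearson on the log scale, and state Spearman as the sensitivity analysis. If a normality check is kept, use Shapiro-Wilk (gated power about 71% in the same model) and apply one scale to all versions of a marker that are compared, whether averaged or single, measured or spot-estimated.

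The cost is one or two sentences and no extra data. There are two small downsides: coefficients are read on the log scale, and a marker that is in fact close to normal would be logged as well.

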## 1. Summary

Folate intake may be marginal in subgroups of the western population, and a noninvasive method for the screening of folate status would allow for easier and less cumbersome assessment, than the identification via the established markers serum or red blood cell folate concentration. Such a method could be applied in epidemiological studies and in large clinical trials including children.

Markers, which seem suitable for this purpose are urinary excretion of formiminoglutamate (FIGLU) and para-aminobenzoylglutamate (p-ABG), which are an intermediate of folate dependent conversion of histidine to glutamate or a catabolite of folate, respectively. In case of folate deficiency urinary excretion of FIGLU is increased after a histidine load and clinical trials have shown increased total p-ABG excretion after increased folic acid intake. Thus we plan to test the suitability of these markers by analyzing red blood cell and serum folate concentration as well as 24-h urinary excretion of FIGLU and p-ABG in 50 healthy, adult men. The participants will deliver a spot urine sample and a blood sample at their first study visit, while at the second visit (21 days later) they will provide the collected urine of the last 24 hours, a further spot urine sample and a second blood sample. This enables testing of short time variation of circulating markers. Furthermore, this enables a comparison of the results obtained by direct measurement of 24-h urinary excretion with estimation of 24-h excretion from a single sample with adjustment via urinary creatinine concentration. These measurements are used to evaluate the applicability of urinary FIGLU and p-ABG as indicators of folate status for screening purposes.

In the supplementation part of the study from those participants in the lowest quartile of RBC folate level and from those in the highest quartile of RBC folate 10 subjects will be selected each, for participation in a folic acid supplementation trial. These subjects will consume daily a 400 µg folate supplement for 12 weeks. Their urinary and blood folate markers will be analysed after 6 weeks and 12 weeks to evaluate the suitability of FIGLU and p-ABG excretion as indicators of folate level in supplementation studies. The relationship between circulating and urinary markers will be statistically evaluated by analysis of correlation and by receiver operator characteristics analysis.

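### A better correlation of the two-visit averages cannot show that time trends in blood folate were attenuated, because random within-subject error alone also produces it

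*Protocol*

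**What the plan says.** The Summary gives the repeated blood sample a purpose of its own: "This enables testing of short time variation of circulating markers". The two baseline visits are three weeks apart.

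Section 9 gives the reasoning. The blood markers are said to "undergo not only random variation, but there might be trends over time, after changes of dietary habits or physiological status", so random variation and trend are named as two different things. It continues: "The effect of these trends should be attenuated by application of the average values of two measurements taken at different time points". It then names the sign by which this is to be recognised: "This should become obvious from a better correlation of the averaged values compared to the individual values". No margin, test or interval is attached to that comparison.

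On the method, section 9 states: "Correlation analysis will be performed according to Pearson or Spearman". I take the correlation in question to be that between a blood folate marker and a urinary marker, since this is the main analysis of that section.

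The protocol states no other analysis of the two baseline blood values. The repeated-measures analysis of variance in section 9 uses high or low folate group as a factor. It therefore concerns the men in the supplementation part, not the 50 men of the correlation study.

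**The concern.** The text separates trend from random variation and then offers, as the visible sign that trend has been dampened, something that random variation produces unaided. Averaging two noisy readings of a stable quantity makes the result more reliable, and a more reliable variable correlates better with anything it is truly related to. No trend is required.

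What is at stake is the secondary aim in the Summary. If the correlation comparison is the only use made of the two baseline values, a report could say that short-term trends were present and were removed by averaging when the data say nothing of the kind. It could equally miss a real shift in the whole group between visits, because correlations do not register one.

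**Working it through.** **Inputs.** From the protocol: n = 50 and a target correlation of 0.35 (section 5.1), two baseline visits, Pearson or Spearman (section 9). Section 9 attaches no figure to the averaging argument, so there is none to reproduce. Assumed, because the protocol does not give it: the reliability R of a single blood folate value, meaning the between-subject share of its variance, over 0.5 to 0.9.

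**1. Random error only, no trend.** If rho is the correlation of the urinary marker with the true blood level:

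- single visit: r_single = rho × sqrt(R)
- average of two visits: r_avg = rho × sqrt(2R/(1+R))
- ratio: r_avg / r_single = sqrt(2/(1+R))

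With r_single = 0.35:

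| R | factor | r_avg |
|---|---|---|
| 0.5 | sqrt(2/1.5) = 1.155 | 0.40 |
| 0.7 | sqrt(2/1.7) = 1.085 | 0.38 |
| 0.8 | sqrt(2/1.8) = 1.054 | 0.37 |
| 0.9 | sqrt(2/1.9) = 1.026 | 0.36 |

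The expected correlation rises in every row although no trend is present.

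**2. Trend common to all men.** Adding a constant to every visit 2 value changes neither deviations from the mean nor ranks, so Pearson and Spearman are unchanged. In simulation with rho = 0.35 and R = 0.8, the mean correlations (visit 1 / visit 2 / average) are 0.310 / 0.310 / 0.327 without a shift and 0.309 / 0.310 / 0.326 with a shift of one between-subject SD.

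**3. Trends that differ between men, no measurement error.** With rho = 0.35 and individual changes scattered symmetrically around a stable level, the simulated means are:

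- change SD 0.5 (in between-subject SDs): 0.337 / 0.336 / 0.347
- change SD 1: 0.311 / 0.311 / 0.348

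The correlation rises, as it does under random error. If the urinary marker instead follows the visit 2 level, change SD 1 gives 0.245 / 0.347 / 0.329. The average then beats visit 1 but falls below visit 2, so a real trend can also make the averaged correlation worse than one of the individual ones.

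**4. How often the sign appears at n = 50 with no trend.** Simulation, 20,000 samples per value of R, single-visit correlation 0.35, R from 0.5 to 0.9. The averaged correlation exceeds

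- that of a given single visit in about 62-79% of samples;
- those of both visits in about 23-58%;
- the mean of the two in more than 99%.

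The third result is close to an identity. With equal SDs at the two visits, r_avg = (r1 + r2)/sqrt(2(1 + r12)), which exceeds (r1 + r2)/2 whenever r1 + r2 is positive and r12 is below 1. The SD of the difference between the averaged and the visit 1 correlation is 0.03 to 0.07, as large as or larger than the expected gain of 0.01 to 0.05.

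**5. What the same data can show.** The visit 2 minus visit 1 difference has SD sqrt(2(1/R − 1)) in units of the between-subject SD: 1.41 at R = 0.5 and 0.93 at R = 0.7. For an assumed common shift of 0.5, the shift divided by its standard error is 0.5 × sqrt(50)/1.41 = 2.5 and 0.5 × sqrt(50)/0.93 = 3.8. A paired t-test then detects it in about 69% and 96% of samples. The correlation comparison carries no information about that shift.

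**The case against.** The strongest reply is that section 9 states a rationale, not a decision rule. Its sentence can be read as saying only that the benefit of averaging will be visible, and step 1 confirms that averaged values should correlate better. The trends it has in mind follow changes in diet or physiological status and so plausibly differ between men. Averaging does dampen such trends, and the expectation is then right in direction. Nothing later depends on the comparison: participants for supplementation are chosen on RBC folate at the first appointment (section 6.2), and neither the sample size nor the primary criterion uses it. Finally, the choice among ICC, CV and intervals is ordinary SAP material.

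Much of this stands. A reader might infer that the protocol's reasoning gives a wrong answer; the text does not support that, since under individual trends the expected rise can occur for the stated reason. A reader might also infer that trends would be confirmed almost every time. That holds only against the mean of the two single-visit correlations, a comparator the protocol does not name, and it is nearly automatic there.

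What does not fall away is that section 9 itself distinguishes trend from random variation and then ties the dampening of trend to a sign that cannot distinguish them. This is a stated inference, not a detail left to the SAP, and no other analysis stated for the two baseline values serves the purpose given in the Summary.

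**Conclusion.** The point holds as one of non-specificity. A better correlation of the averages is expected from random error alone (a gain of about 15% at R = 0.5 and 3% at R = 0.9), can arise from individual trends, and is blind to a common trend. Whether it appears in one sample of 50 is also largely a matter of chance. It therefore neither shows nor excludes trends.

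The algebra needs only independent errors of equal variance at the two visits. The percentages rest on the assumed range of R, normal data and a single-visit correlation of 0.35. The averaging itself is sound. The consequence is limited to the secondary aim of describing short-term variation and does not reach the assessment of the urinary markers.

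**What to change.** In section 9:

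- Keep the two-visit average as the more reliable blood value for the correlation with the urinary markers.
- Remove the inference about trends from the comparison of averaged with individual correlations.
- For serum and RBC folate in all men with both baseline visits, report the mean visit 2 minus visit 1 difference with a 95% CI (common trend), and the within-subject SD or CV and the intraclass correlation (total within-subject variation).
- State that two time points cannot fully separate individual trends from random within-subject variation, so the within-subject figures describe the two together.

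The cost is a few lines of text and analysis on data already planned, with no extra visits or samples. The limit in the last item remains and should be stated as a limitation.

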Sciences, University of Toronto, Canada; and [name], Department of Pharmacology, University of Bergen, Norway). 24-h urinary excretion of folate was reported to decline significantly in Mexican American men within 6 weeks after onset of a controlled diet, which provided 418 µg/d of dietary folate equivalents (Solis et al, 2008). At the same time significant decreases of serum and RBC folate were observed. Although this suggests applicability of urinary folate excretion as an indicator of folate status, there is large interpersonal variation in the amount excreted and excretion might depend on methyltetrahydrofolate reductase genotype (Yang et al, 2005; Guinotte et al, 2003). This seems to limit the predictive value of folate excretion for folate status. Urinary excretion of FIGLU is known to be elevated after a histidine load, in case of folate deficiency (Cooperman et al, 2002). Although in a previous study no significant correlation of FIGLU excretion, with other markers of folate status could be demonstrated (Pietrzik et al, 1980), improved analytical techniques (LC-MS/MS) warrant a reconsideration. However, the most promising biomarker of folate status in urine might be folate catabolites (Bailey et al, 1999). Although not polyglutamated folate can efflux from the cell either directly after entering the cell or after hydrolysis by γ-glutamylhydrolase, non reversible folate catabolism proceeds via non enzymatic or potentially enzyme catalysed cleavage of the C9-N10 bond of dihydrofolate, yielding a pterin aldehyde and p-aminobenzoylglutamate (Suh et al, 2001). While the pterin residue is retained in the liver and only slowly released, the export of p-aminobenzoylglutamate (p-ABG) out of the cells is facilitated by removal of the polyglutamate and the majority of p-ABG is acetylated at the amino group catalysed by arylamine N-acetyltransferase. Acetylated p-ABG (Ap-ABG) does not accumulate in cells and is rapidly excreted in urine (Murphy et al, 1976). In rats Ap-ABG concentration in urine is considered a reliable marker of folate status and turnover (Wang et al, 1994). Results in humans are not fully supporting the hypothesis that urinary total p-ABG is a good indicator of folate status and/or intake, because catabolite excretion might reflect changed intake only after some delay as total p-ABG (Ap-ABG and p-ABG) originates from slow turnover pools (Gregory, III et al, 2000). Thus, effects of short term interventions might not be detected by the analysis of urinary p-ABG, but a correlation with a long term marker such as RBC folate, can be assumed. Furthermore, tracer experiments with deuterated folic acid demonstrated that turnover of folate pools in humans increases with increasing intake, thus an increased catabolite excretion can be expected (Gregory, III et al, 1998). In a study in postmenopausal women, involving 7 week periods of folate depletion (intake 120 µg/d) and repletion (intake 200 µg/d or 400 µg/d) significant correlations between serum folate, RBC folate and urinary excretion of catabolites were observed (Wolfe et al, 2003). These findings were obtained with 24h urine collections, thus it will be tested whether FIGLU or total p-ABG concentrations in spot urine samples can be extrapolated to 24 h excretion via urinary creatinine concentration (Bingham et al, 1988). This is of

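### Section 9 checks spot-urine extrapolation only indirectly, through RBC folate; with 50 subjects a missing difference does not show that extrapolation is adequate, and the paired samples allow a direct check

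*Protocol*

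**What the plan says.** Protocol section 9 gives the reasoning for the 24-h collection. If short-term variation makes creatinine extrapolation inadequate, "there should be a closer relationship between the measured 24 h excretion of p-ABG and FIGLU with RBC folate" is expected, closer "than between the 24 h excretion estimated from the spot urine sample and RBC folate". The same section compares markers by area under the ROC curve, with the lowest quartile of RBC folate as reference, for both measured and estimated 24-h excretion. Both routes go through RBC folate. Neither a test of the difference in correlations nor a direct spot-versus-24-h analysis is named.

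Elsewhere a direct look is announced without a method. The Summary says the design permits a "comparison of the results obtained by direct measurement of 24-h urinary excretion with estimation of 24-h excretion from a single sample". Section 3 says "it will be tested whether FIGLU or total p-ABG concentrations in spot urine samples can be extrapolated to 24 h excretion via urinary creatinine" concentration.

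Section 6.1 provides the data: at the second appointment each subject hands in a 24-h collection with recorded volume and also gives a spot sample. Section 6.2 attaches a decision: spot samples are to be collected in the intervention study in place of 24-h urine if the correlation study finds them useful.

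On size, section 5.1 states that "50 subjects will be enrolled into the correlation study", on the premise that "a correlation of at least 0.35 would be sufficient to use urinary total p-ABG or FIGLU as markers".

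**The concern.** Whether a spot estimate reproduces 24-h excretion is a question about two measurements on the same person. Section 9 answers it by comparing two modest, mutually dependent correlations with a third variable. The study was sized to distinguish one correlation from zero, not to distinguish two correlations from each other.

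The section 9 criterion is informative when a difference appears. When none appears, the result fits an adequate spot estimate and also a poor one. The criterion is weakest where the marker is weak: if 24-h excretion hardly tracks RBC folate, both correlations lie near zero and even a poor spot estimate shows no shortfall. Section 3 reports an earlier study in which FIGLU did not correlate significantly with other folate markers, so this case is not remote.

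A correlation also cannot show systematic error. A spot estimate wrong by a constant factor has the same correlation and ROC area. That matters if a cut-off derived from one kind of sample is applied to the other, and section 10 regards cut-off values as a precondition for screening use.

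At stake is the statement that spot urine can stand in for 24-h excretion, and with it the section 6.2 decision to drop 24-h collection.

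**Working it through.** **Inputs.** From section 5.1: n = 50; r = 0.35 as the smallest useful correlation, used here as the correlation of measured 24-h excretion with RBC folate. Assumed, because the documents give no value: ρ, the spot-to-24-h correlation, from 0.5 to 0.9. Also assumed: the spot estimate is 24-h excretion plus error unrelated to RBC folate, so r(spot, RBC) = r × ρ.

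**The plan's own figure.** Section 5.1 states 49 subjects. By Fisher's z, n = ((z_α + z_β)/atanh(r))² + 3, with atanh(0.35) = 0.3654:
- one-sided α 0.05: ((1.645 + 0.842)/0.3654)² + 3 = 49.3, which matches;
- two-sided α 0.05: ((1.960 + 0.842)/0.3654)² + 3 = 61.8.

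The sidedness is not stated and is a separate matter. Here the point is that the calculation concerns r = 0.35 against zero only.

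**Power of the indirect comparison.** For two correlations r₁ and r₂ sharing one variable (Dunn-Clark/Steiger):

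c = [ρ(1 − r₁² − r₂²) − ½r₁r₂(1 − r₁² − r₂² − ρ²)] / [(1 − r₁²)(1 − r₂²)]

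SE = √[(2 − 2c)/(n − 3)], and power ≈ Φ(d − 1.96) + Φ(−d − 1.96), with d = [atanh(r₁) − atanh(r₂)]/SE.

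For ρ = 0.5: r₁ = 0.35, r₂ = 0.175, c = 0.476, SE = √(1.047/47) = 0.149, d = (0.3654 − 0.1768)/0.149 = 1.26, power 24%.

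For ρ = 0.9: r₂ = 0.315, c = 0.888, SE = √(0.223/47) = 0.069, d = (0.3654 − 0.3261)/0.069 = 0.57, power 9%.

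| ρ | r(spot, RBC) | Power, two-sided | Power, one-sided | Spot looks equal or better | n for 80% power, two-sided |
|---|---|---|---|---|---|
| 0.5 | 0.175 | 24% | 35% | 10% | 235 |
| 0.7 | 0.245 | 17% | 25% | 16% | 385 |
| 0.9 | 0.315 | 9% | 14% | 28% | 1135 |

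Simulation of the Williams test agrees (25%, 17% and 9% two-sided). The fifth column comes from simulation and applies if the two estimates are simply ranked.

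**Sensitivity, two-sided, ρ from 0.9 to 0.5.** r = 0.4: 10–31%; r = 0.5: 14–49%; r = 0.6: 21–69%. If the spot correlation is not tied to r × ρ, power can be higher: 0.35 against 0.20 at ρ = 0.9 gives 68%.

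**What the paired values give at n = 50.** The 95% interval for ρ is tanh(atanh(ρ) ± 1.96/√47), half-width 0.286 on the z scale:
- ρ = 0.5: 0.26 to 0.68
- ρ = 0.7: 0.52 to 0.82
- ρ = 0.9: 0.83 to 0.94

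In an agreement analysis the mean difference is known to ±2.01/√50 = ±0.28 SD of the differences, and each limit of agreement to ±1.96√(1/50 + 1.96²/(2 × 49)) = ±0.48 SD.

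For illustration, against an assumed benchmark of ρ = 0.9 (one-sided 2.5%), a direct analysis shows a shortfall with 99% power if ρ is 0.7 and 73% if it is 0.8. At r = 0.35 the indirect comparison has 17% and 13% in these cases.

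**The case against.** **Spot urine has its own test.** A reader might infer that the whole case for spot urine rests on this low-power comparison. The documents do not support that. Hypotheses (a) and (b) in section 4 require the spot-extrapolated excretion itself to correlate with RBC and plasma folate. Section 9 makes the obtained coefficients the primary criterion and adds ROC analysis. In the poor case above (ρ = 0.5, spot correlation 0.175), the spot estimate would reach two-sided significance with RBC folate in only about 23% of studies. It would be both significant and at least as good as 24-h urine in about 6%. This stands and limits the point to extrapolation.

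**No test is named.** Section 9 does not say that a non-significant difference means adequacy. The power figures describe a formal test of its reasoning; if estimates are only ranked, the order is right in 90% of studies at ρ = 0.5 and 84% at ρ = 0.7. This stands, but neither route turns a missing difference into evidence of adequacy.

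**The 9% and 28% belong to a mild shortfall** (0.315 against 0.35), where an error costs little. True; the 17–25% figures concern a materially worse spot measure.

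**A direct comparison is announced, and the choice of statistic may be left to an analysis plan.** It would therefore be wrong to say that the protocol never considers one. But section 9 does write down a criterion for extrapolation, and that criterion is the indirect one.

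**Agreement is a different question from marking folate status.** This defeats making agreement the primary spot-urine analysis. It does not defeat adding it, because section 3 promises a test of extrapolation to 24-h excretion and section 6.2 acts on spot usefulness.

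**Conclusion.** The point holds for the adequacy of creatinine extrapolation and not beyond it. As written, section 9 can reveal a poor spot estimate by chance or when the shortfall is large, but it cannot show a good one. With r = 0.35, ρ of 0.5 to 0.9, independent spot error and n = 50, two-sided power is about 25% down to 9%; it is 49% down to 14% if r is 0.5. The values of ρ and the error model are assumptions, and 0.35 is the protocol's minimum useful correlation rather than an expected one, so these figures are conditional. Two parts need none of these assumptions: a missing difference is not proof of adequacy, and a constant bias is invisible to correlation and ROC area. I would treat this as a cheap improvement, not a flaw in the design.

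**What to change.** In section 9, assess extrapolation directly on the paired second-appointment values, separately for total p-ABG and FIGLU. Analyse log(estimated/measured 24-h excretion), reporting mean bias and 95% limits of agreement, together with a concordance or intraclass correlation and its confidence interval.

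Keep the comparison of RBC-folate correlations as supportive for this question, with a test for dependent correlations and a confidence interval for the difference. State that the absence of a difference will not be read as adequacy.

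Leave the correlation of the spot estimate with RBC and plasma folate, and the ROC analysis, as the main test of spot urine as a folate marker.

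The cost is slightly more analysis work and some wording. No further samples or subjects are needed.
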